# Cycling in primary progressive multiple sclerosis (CYPRO): study protocol for a randomized controlled superiority trial evaluating the effects of high-intensity interval training in persons with primary progressive multiple sclerosis

**DOI:** 10.1186/s12883-023-03187-6

**Published:** 2023-04-22

**Keywords:** Multiple sclerosis, Primary progressive multiple sclerosis, High-intensity interval training, Physical fitness, Cardiorespiratory fitness, Serum neurofilament light chain, Glial fibrillary acidic protein, Kynurenine pathway

## Abstract

**Background:**

Primary progressive multiple sclerosis (PPMS) is the least prevalent multiple sclerosis (MS) phenotype. For persons with PPMS (pwPPMS), pharmacological treatment options are limited. As a complementary non-pharmacological treatment, endurance training improves the health-related quality of life (HRQoL), numerous MS symptoms, and MS-related performance impediments. High-intensity interval training (HIIT) has been shown to induce superior effects compared to moderate-intensity continuous training (MCT). As current evidence is based on MS samples with mixed phenotypes, generalizability to pwPPMS remains unclear.

**Methods:**

CYPRO is a parallel-group, single-center, and single-blind randomized controlled superiority trial evaluating the effects of HIIT compared to MCT in pwPPMS. Sixty-one pwPPMS are randomized (1:1) to perform volume-matched HIIT or MCT sessions on bicycle ergometers two to three times per week in addition to standard rehabilitative care during their three-week inpatient stay at Valens rehabilitation clinic, Switzerland. Standard rehabilitative care comprises endurance and strength training, physiotherapy, and occupational therapy. HIIT sessions include six 90-second intervals at 95% peak heart rate (HR_peak_), interspersed by 90-second active breaks with unloaded pedaling, aimed to reach 60%HR_peak_. MCT represents the standard treatment at Valens rehabilitation clinic and is performed as continuous cycling at 60%HR_peak_ for the duration of 26 minutes. The primary outcome is cardiorespiratory fitness, assessed as peak oxygen consumption (V̇O_2peak_) during cardiopulmonary exercise testing (CPET). Secondary outcomes include peak power output during CPET, walking capacity, cognitive performance, HRQoL, fatigue, anxiety and depressive symptoms, and blood-derived biomarkers (e.g., serum neurofilament light chain, glial fibrillary acidic protein, kynurenine pathway metabolites) related to MS pathophysiology. All outcomes are assessed at baseline and discharge after three weeks. Venous blood sampling is additionally performed immediately and two hours after the first HIIT or MCT session.

**Discussion:**

CYPRO will expand current knowledge on symptom management and rehabilitation in MS to the subpopulation of pwPPMS, and will contribute to the exploration of potential disease-modifying effects of endurance training in MS. The superiority design of CYPRO will allow deriving explicit recommendations on endurance training design in pwPPMS that can be readily translated into clinical practice.

**Trial registration:**

CYPRO has been prospectively registered at ClinicalTrials.gov on 8 February 2022 (NCT05229861).

**Supplementary Information:**

The online version contains supplementary material available at 10.1186/s12883-023-03187-6.

## Background

Multiple sclerosis (MS) is a chronic inflammatory, demyelinating, and neurodegenerative disease of the central nervous system (CNS) that globally affects approximately 2.8 million people [1, 2]. In most cases, MS initially manifests as relapsing-remitting phenotype (RRMS) and frequently transitions into secondary progressive MS (SPMS) after several years. Primary progressive MS (PPMS) is the least prevalent MS phenotype, affecting 10–15% of persons with MS (pwMS) [3]. PPMS is characterized by gradual disability worsening from disease onset [4]. Disability worsening is considered to primarily evolve from neurodegenerative aspects of the MS pathophysiology, such as neuroaxonal damage, astrocytic gliosis, and mitochondrial failure due to increased oxidative stress, all of which culminate in pronounced brain and spinal cord atrophy [3, 5]. In contrast to neuroinflammation predominating in RRMS, neurodegeneration is largely unresponsive to current disease-modifying treatment [3]. In PPMS, pharmacological treatment is limited to the humanized anti-CD20 antibody ocrelizumab. However, the benefits of ocrelizumab on disease progression and brain atrophy are diminished in older persons with PPMS (pwPPMS), or those presenting with low residual inflammation [6].

Alongside ongoing efforts to improve disease-modifying treatment in pwPPMS, optimization of complementary non-pharmacological treatment options is recognized as essential to maintain and improve the health-related quality of life (HRQoL) in pwPPMS [7]. Accordingly, the International Progressive MS Alliance called upon action, proposing symptom management and rehabilitation as one key priority area for research in progressive MS [8]. In line with the proposed goals for MS therapies, endurance training qualifies as an effective means to improve HRQoL, numerous MS symptoms, such as walking impairment or fatigue, and MS-related performance impediments, such as reduced cardiorespiratory fitness, in pwMS [8–10]. Beyond that, high-intensity interval training (HIIT) has been described to beneficially modulate systemic concentrations of blood-derived biomarkers relevant to PPMS pathophysiology. For example, an acute HIIT session reduced concentrations of serum neurofilament light chain (sNfL), serving as a surrogate marker of disease progression, neuroaxonal damage, and CNS atrophy [11, 12]. Additionally, HIIT has been shown to shift systemic concentrations of neurotoxic and pro-oxidant metabolites towards neuroprotective metabolites of the immunomodulatory and neuroactive kynurenine pathway (KP) [11, 13].

However, results have been obtained from mixed samples, dominated by RRMS phenotype. The generalizability of training designs and the desired beneficial effects of endurance training on the subpopulation of pwPPMS remains unclear, given that PPMS presents with distinct clinical features, such as progressive spastic paraparesis as a hallmark symptom [14, 15]. Owing to the high prevalence of progressive spastic paraparesis, particularly pwPPMS may be prone to physical deconditioning, which is indicated by low cardiorespiratory fitness. As cardiorespiratory fitness is associated with HRQoL, walking impairment, cognitive performance, fatigue, and potential CNS tissue sparing in pwMS, improvement of cardiorespiratory fitness represents a key research outcome in MS trials and constitutes a central target in MS rehabilitation [10, 16].

With the randomized controlled trial CYPRO (CYcling in Primary PROgressive Multiple Sclerosis), we present a novel approach to validate the established mixed-sample effects of HIIT and moderate-intensity continuous training (MCT) on cardiorespiratory fitness and a comprehensive set of further MS-relevant outcomes in a sample that is exclusively composed of pwPPMS.

## Methods

This manuscript of a study protocol was designed in accordance with the Standard Protocol Items: Recommendations for Interventional Trials (SPIRIT) 2013 Statement, the Template for Intervention Description and Replication (TIDieR) checklist, and the World Health Organization’s Trial Registration Data Set (Version 1.3.1) [17–19]. The completed SPIRIT and TIDieR checklists are provided as Supplementary material 1 and Supplementary material 2. 

### Aim, study design, and setting

CYPRO is a parallel-group, single-center, and single-blind randomized controlled superiority trial that is performed at the Valens rehabilitation clinic, Switzerland.

The aims of CYPRO are described as the following:

1. Primary aim: To investigate the effects of HIIT compared to MCT on cardiorespiratory fitness, as indicated by peak oxygen consumption (V̇O_2peak_).

2. Secondary aims: To investigate the effects of HIIT compared to MCT on peak power output (PPO), walking capacity, cognitive performance, HRQoL, fatigue, anxiety and depressive symptoms, and blood-derived biomarkers related to MS pathophysiology. Additionally, CYPRO aims to investigate the acute effects of a single HIIT session compared to a single MCT session on changes in blood-derived biomarkers.

HIIT represents the experimental condition that is hypothesized to be superior to the standard treatment MCT as an active comparator. The study design and flow of participants are illustrated in Fig. 1.

**Fig. 1 Fig1:**
[figure not shown]
Study design and flow of participants Abbreviations: PPMS= primary progressive multiple sclerosis; pwPPMS= persons with PPMS; HIIT: high-intensity interval training; MCT: moderate-intensity continuous training; EDSS= Expanded Disability Status Scale; CPET= cardiopulmonary exercise testing. Created with BioRender.com

### Sample size calculation

Sample size calculation for the estimated effect of HIIT or MCT on the primary outcome V̇O_2peak_ was performed using G*Power software (Version 3.1.9.7, Heinrich Heine Universität, Düsseldorf, Germany) [20]. Estimating a drop-out of 15%, a total of 61 participants (HIIT: *n*= 30, MCT: *n*= 31) was found to be sufficient to identify a small to moderate effect (*ES* ≥ 0.15) in ANOVA analysis on 2 group (HIIT vs. MCT) * 2 time (T_0_ vs. T_4_) interaction. Power was set at 80% and alpha at 0.05. Correlation among repeated measures was set at 0.6.

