#### Cardiorespiratory fitness

V̇O_2peak_ is assessed by CPET on a bicycle ergometer (ergometrics er800s, ergoline GmbH, Bitz, Germany). CPET is performed in a fasted state between 8:00 and 9:00 AM and follows a ramp-type protocol. The ramp-type protocol consists of (a) a resting state measurement without pedaling while participants are sitting on the bicycle ergometer (3 minutes); (b) subsequent pedaling at 20 watts (3 minutes); (c) the testing phase with a progressive increment of 5 to 10 watts per minute until subjective exhaustion (8-12 minutes); (d) followed by a cool-down of unloaded pedaling (3 minutes). HR is continuously monitored. Blood pressure and RPE (Borg CR-10 scale) are assessed every two minutes and within the last ten seconds of the test.

V̇O_2_ is monitored by direct and continuous measurements (breath by breath) by ergospirometry (Vyaire Medical, Vyntus CPX, Illinois, USA). V̇O_2peak_ is defined as the highest 15-second averaged V̇O value when the following criteria are attained: respiratory equivalent ratio > 1.10; HR_peak_ within 10 min^−1^ of the age-predicted maximum and Borg-CR-10 rating > 8.5 [31]. The absolute V̇O_2peak_ value (mL · min^−1^) is divided by bodyweight (kg) to obtain the relative V̇O_2peak_ value (mL · min^− 1^ · kg^− 1^) as the primary outcome.

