### Statistical analysis

Statistical analyses are performed according to the intention-to-treat principle. Descriptive statistics will be reported as arithmetic mean (*M*) and standard deviation (*SD*) for continuous data, and as absolute number and percentage (*%*) for categorical data for the total sample, and separated by group. Outcome data will be checked for normality (Shapiro-Wilk test) in advance. If necessary, analyses will be adjusted accordingly. If missing values are < 5%, ANCOVA will be performed to detect time*group interaction effects and main effects of time. In that case, effect sizes will be calculated as partial eta squared (*pη*^*2*^). Otherwise, a baseline-adjusted Mixed Model for Repeated Measures (MMRM) approach, with group, time and the group × time interaction as fixed effects (type III sums of squares, CS covariance structure over time) is used to assess between-group differences over time. Bonferroni-corrected pairwise comparisons of estimated marginal means of the group × time interaction are computed. Effect sizes will be reported as Cohen’s *d* with 95% confidence interval (*CI*). For all analyses, the level of significance is set at *p* = .05. Within-group differences and between-group differences are depicted as point estimates and measures of variability for all outcomes. Bivariate correlation analyses will be conducted to determine potential associations between changes in V̇O_peak_, PPO, walking capacity, cognitive performance, HRQoL, fatigue, anxiety and depressive symptoms, and blood-based biomarkers using Pearson’s *r*. All statistical analyses will be conducted with IBM SPSS Statistics for Windows (Version 29.0., IBM Corp., Armonk, New York, USA). Besides the final analysis, one interim analysis will be performed upon collection of 50% of participant data (HIIT: *n* = 15, MCT: *n* = 16).

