As a prospective study that is well-powered for pwPPMS, CYPRO is a novel approach accounting for the distinct features of pwPPMS, that besides PPMS-relevant performance indices and patient-reported outcomes measures, includes blood-derived biomarkers, such as sNfL or GFAP, that are closely related to neurodegenerative aspects of PPMS pathophysiology. Herewith, CYPRO will not only expand knowledge on symptom management and rehabilitation, but will also contribute to the exploration of potential disease-modifying effects of endurance training in MS. The superiority design of CYPRO will allow deriving explicit recommendations on endurance training design in pwPPMS that can be readily translated into clinical practice.

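### The planned effect (ES 0.15, read as Cohen's f) is a 0.60 SD between-arm difference in VO2peak change, medium to large on the scales to be reported, and 61 participants give it about 66% to 73% power, not 80%

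*Protocol article*

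**What the plan says.** The primary outcome is body-weight-relative VO2peak: the absolute value is divided by weight "to obtain the relative V̇O_2peak_ value (mL · min^− 1^ · kg^− 1^) as the primary outcome" (Cardiorespiratory fitness).

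The Sample size calculation section used G*Power 3.1.9.7. It allows 15% drop-out and says that a total of 61 participants (30 and 31) "was found to be sufficient to identify a small to moderate effect (*ES* ≥ 0.15) in ANOVA analysis on 2 group (HIIT vs. MCT") by 2 time points (baseline and discharge), tested as the interaction. The other inputs are "Power was set at 80% and alpha at 0.05" and "Correlation among repeated measures was set at 0.6". The section does not say which effect-size metric ES is.

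The Statistical analysis section gives two branches. With fewer than 5% missing values, ANCOVA is used and partial eta squared is reported. Otherwise a baseline-adjusted mixed model is used, and "Effect sizes will be reported as Cohen’s *d* with 95% confidence interval (*CI"). Neither branch reports Cohen's f.

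The Discussion adds: "As a prospective study that is well-powered for pwPPMS, CYPRO is a novel approach accounting for the distinct features of pwPPMS".

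**The concern.** The words small to moderate and the figure of 80% tell the reader how small a benefit of HIIT over MCT the trial can find. Two things blur that message.

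- **Scale.** The usual f benchmarks (0.10 small, 0.25 medium) match the d benchmarks (0.2, 0.5) through f = d/2, which holds for two groups compared once. On a 2 x 2 group-by-time interaction, the same f needs a raw between-arm difference twice as large. Results will be reported as d or partial eta squared, so the planning label and the reported effect will not be on the same scale.
- **Power.** The 80% does not follow from the stated inputs, even at f = 0.15.

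At stake is the reading of a non-significant primary result. Set against this sample size statement, it could be taken as evidence against a benefit that the trial had little chance of detecting.

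**Working it through.** **Inputs (protocol article).** ES 0.15; 2 groups, m = 2 times; correlation rho = 0.6; alpha 0.05; power 80%; drop-out 15%; N = 61; drop-outs not replaced (Compliance section). Completers: 61 x 0.85 = 51.85, taken as 52. Assumptions: ES is Cohen's f in G*Power's default definition for the within-between interaction, and the 1-df F test is equivalent to a two-sided t test.

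**1. The plan's own figure.** Noncentrality is lambda = f² x N x m/(1 - rho) = 0.0225 x 2/0.4 x N = 0.1125 N, with df 1 and N - 2.

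| N analysed | lambda | power at f = 0.15 |
|---|---|---|
| 52 | 5.85 | 66% |
| 61 | 6.86 | 73% |
| 72 | 8.10 | 80% |

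So 80% needs 72 evaluable, or 72/0.85 = 84.7, i.e. 85 enrolled. The stated 61 is not reproduced. Variants do not recover it either:

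- one-sided equivalent: 58 evaluable, 69 enrolled
- rho 0.7: 56 and 66
- G*Power's SPSS and Cohen effect-size options: 354 and 352 evaluable

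Only a changed effect comes near: f = 0.18 (52 evaluable, 62 enrolled), or ES read as partial eta squared 0.15 under the SPSS option (50 and 59). The second is a large effect and does not use the stated correlation.

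**2. What f = 0.15 means.** A between-arm difference in change of delta puts ±delta/4 in each cell, so f = delta/(4 SD) and delta = 4 x 0.15 = 0.60 SD of VO2peak. Check, per participant: delta²/(8(1 - rho)) = 0.36/3.2 = 0.1125, as above.

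- SD of change = sqrt(2 x 0.4) = 0.894 SD, so d = 0.60/0.894 = 0.67.
- Against the ANCOVA residual SD, sqrt(1 - 0.36) = 0.80, d = 0.75.
- Partial eta squared = 0.1125/1.1125 = 0.10. A medium f of 0.25 in a single comparison corresponds to 0.0625/1.0625 = 0.06.

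Both d values lie between the medium (0.5) and large (0.8) benchmarks, and the partial eta squared is above the medium value.

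**3. Power by size of difference, 52 completers.** Interaction as above with f = delta/4. For ANCOVA at T4, lambda = delta² x N/(4(1 - rho²)) with N - 3 df; at 0.60 SD this is 0.36 x 52/2.56 = 7.31.

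| Difference in change (SD) | Interaction | ANCOVA |
|---|---|---|
| 0.2 | 12% | 14% |
| 0.3 | 22% | 26% |
| 0.4 | 35% | 42% |
| 0.5 | 51% | 60% |
| 0.6 | 66% | 76% |

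**4. Difference with 80% power, 52 completers.** Interaction: f = 0.177, delta = 4 x 0.177 = 0.71 SD, d = 0.709/0.894 = 0.79. ANCOVA: 0.634 SD, about 0.64 when rounded up so that power is not below 80%. With all 61 analysed, the interaction figure is f = 0.163, 0.65 SD, d = 0.73.

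**The case against.** - **On the f scale the label is conventional.** A value of 0.15 lies between 0.10 and 0.25, and the section never says d. This stands. A reader might infer that the label is an arithmetic error, but the article does not support that: the label is an unnamed scale that differs from the reporting scales. The numerical failure is in the 80%.
- **The analysis may be more efficient than the sized test.** This stands in part. By ANCOVA with all 61 analysed, power at 0.60 SD is 82%. But the article sized the interaction and assumed 15% drop-out; with 52 completers ANCOVA gives 76%.
- **The range 0.2 to 0.4 SD is the reviewer's choice.** True; the article gives no difference in SD units. One might say that any small-to-moderate benefit would be missed more often than not. That holds for 0.2 to 0.4 SD with 52 completers, but not at 0.5 SD, where power is 51% to 60%.
- **The Cohen's d branch is not certain.** With 15% drop-out counted by participant, the chance of at most 3 of 61 missing is 1.3%. Counted over the 122 baseline and discharge values with baseline complete, up to 6 missing stays under 5%, and that chance is 17%. The article does not fix the denominator. The point does not depend on it, since the effect is above medium on either reported scale.
- **Well-powered in the Discussion may only contrast this sample with earlier mixed-phenotype samples.** That is a fair reading: the phrase is loose and states no effect size. Nor does the article say that a null result will be read as excluding a benefit, and it already promises 95% CIs for Cohen's d.
- **Conversion to mL/min/kg may sit in the full protocol.** Accepted; its absence is not part of this point.

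**Conclusion.** The point holds as a mismatch of scale together with an overstated power. If ES is Cohen's f in G*Power's default definition and the correlation is 0.6, the target is a 0.60 SD between-arm difference in VO2peak change, which is medium to large in the metrics that will be reported. The sized test has about 66% power for it at the assumed drop-out, and 73% with none. Differences of 0.2 to 0.4 SD are well short of 80% under either analysis. The conclusion rests on the f reading, because the metric is unnamed. The only other reading found that comes near 61, partial eta squared 0.15, would make the target larger still and fit the label worse.

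**What to change.** Keep N at 61 and restate what it delivers.

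1. In Sample size calculation, name the metric and replace the present claim with, for example: with about 52 completers, correlation 0.6 and two-sided alpha 0.05, the group-by-time interaction test has 80% power for a between-arm difference in VO2peak change of about 0.71 SD (f about 0.18, d about 0.79 on change scores); baseline-adjusted ANCOVA has 80% power for about 0.64 SD; at f = 0.15 (0.60 SD) power is about 66% and 76% respectively. Naming 0.60 SD while leaving 80% beside it would still be wrong.
2. In the Discussion, limit the well-powered statement to VO2peak differences of that size.
3. State that a non-significant primary result will be interpreted from the 95% CI and not as excluding a small or moderate benefit.

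The cost is a few sentences and a less favourable stated detectable effect. No participants or procedures are added.

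### The sample size of 61 does not follow from its stated inputs: with ES read as Cohen's f, the planned interaction test has about 66% power after 15% drop-out, not 80%

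*Protocol article*

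**What the plan says.** The section on sample size calculation in the protocol article gives a near-complete specification.

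- **Software:** the calculation "was performed using G*Power software (Version 3.1.9.7".
- **Test:** the effect is to be detected "in ANOVA analysis on 2 group (HIIT vs. MCT) * 2 time (T_0_ vs. T_4_) interaction".
- **Effect:** the total of 61 (30 and 31 per arm) "was found to be sufficient to identify a small to moderate effect", given as an ES of at least 0.15. The metric behind ES is not named.
- **Other inputs:** "Power was set at 80% and alpha at 0.05. Correlation among repeated measures was set at 0.6".
- **Drop-out:** 15%, already allowed for in the 61.

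The section on recruitment and randomization confirms that 61 is the number to be recruited. The section on compliance says that people who drop out are not replaced and have no later assessments. The section on statistical analysis plans an ANCOVA if fewer than 5% of values are missing, and otherwise a baseline-adjusted mixed model. The Discussion describes the trial thus: "As a prospective study that is well-powered for pwPPMS".

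**The concern.** A sample size statement that prints its design, effect, alpha, power, correlation and drop-out can be recomputed, and this one does not return 61. Since 61 is the enrolled number and drop-outs have no T4 measurement, the relevant number for power is about 52. On the stated test the chance of missing the target effect is then about 34%, against the 20% that the article implies.

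This is the calculation for the primary outcome, and the Discussion relies on it when it describes the trial's power and the recommendations it expects to derive. If the result is inconclusive, readers need the correct power, or the correct detectable effect, to interpret it.

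**Working it through.** **Inputs, all from the sample size section unless noted**
- k = 2 groups, m = 2 times, within-between interaction
- ES = 0.15, read as Cohen's f under G*Power's default option (assumption)
- alpha = 0.05, F test
- correlation rho = 0.6
- target power 80%
- drop-out 15%; 61 enrolled, so 61 × 0.85 = 51.85, about 52 completers (not replaced and not assessed later, per the compliance section)

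**Formula.** Power comes from the noncentral F distribution with
- lambda = f² × N × m / (1 − rho) = 0.0225 × N × 2 / 0.4 = 0.1125 × N
- df1 = (k − 1)(m − 1) = 1, df2 = (N − k)(m − 1) = N − 2

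**Step 1: try to reproduce 61 at 80%**

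| Evaluable N | lambda | Power |
|---|---|---|
| 52 | 5.85 | 66.0% |
| 61 | 6.86 | 73.1% |
| 71 | 7.99 | 79.6% |
| 72 | 8.10 | 80.1% |

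The requirement is 72 evaluable participants. Inflated for drop-out, 72 / 0.85 = 84.7, so 85 enrolled. The stated 61 falls short even if nobody drops out.

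**Step 2: what 52 completers can detect.** Solving for 80% power at N = 52 gives f of about 0.177 with rho at 0.6. With f kept at 0.15, rho would have to be about 0.71.

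**Step 3: cross-check on the change score.** In this design f = 0.15 is a between-arm difference in change of 4f = 0.60 SD, and the SD of the change is √(2 × 0.4) = 0.894 SD. A two-sample normal approximation needs 35 per arm and gives 67.7% power at 26 per arm, in line with Step 1.

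**Step 4: other readings of the inputs**

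| Reading | Evaluable N for 80% | Enrolled at N/0.85 | Power at 52 |
|---|---|---|---|
| rho = 0.5 | 90 | 106 | 56.4% |
| rho = 0.7 | 55–56 | 65–66 | 78.2% |
| F test at alpha 0.10 (one-sided equivalent) | 57–58 | 68–69 | 77.1% |
| ES as partial eta squared | 12 | 15 | about 100% |
| ES as f² | 13–14 | 16–17 | about 100% |
| G*Power's SPSS or Cohen options for f | over 350 | over 410 | about 18% |

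None of these gives 61.

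**Step 5: baseline-adjusted ANCOVA.** With T0 as covariate, lambda = 0.60² × N / [4 × (1 − 0.6²)], df2 = N − 3. At N = 52, lambda = 7.31 and power is 75.5%. At N = 61, lambda = 8.58 and power is 82.1%. For 80%, 58 evaluable (69 enrolled) are needed. At 52 completers the difference detectable with 80% power is about 0.63 SD.

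**Step 6: where 61 may come from.** 72 × 0.85 = 61.2. Subtracting 15% from the required 72 returns the printed total with every other input unchanged. The article does not show this step, so it is a conjecture.

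**The case against.** Four points deserve weight.

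1. **The metric is assumed.** The article prints ES, not f, so the 66% depends on a reading. That stands, and the result should carry the condition. The reading is nevertheless the natural one: f is the G*Power ANOVA metric, it fits the verbal label, and the alternatives tried are much further from 61.

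2. **The planned analysis is more efficient than the test that was powered.** If the ANCOVA or mixed model adjusts for T0, the shortfall is about 5 points, not 14. This softens the point without removing it. The 82% figure needs all 61 to be evaluable, which contradicts the article's own 15% drop-out, and the sample size section claims power for the ANOVA interaction.

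3. **The effect-size label.** A reader might infer that calling 0.15 small to moderate is itself an error, because it corresponds to 0.60 SD between arms. The documents do not support that: on the conventional f scale (0.10 small, 0.25 medium) the label is fair. Adding the SD equivalent is a clarification, not a correction.

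4. **The origin of 61.** A reader might infer that 61 can arise only if a different f or correlation was entered. That does not follow, since 72 × 0.85 = 61.2 on the printed inputs. Nor do the documents show that the drop-out was in fact applied in the wrong direction.

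The statement about power in the Discussion may also be meant mainly as a contrast with earlier mixed-phenotype samples. It still makes a claim that the calculation does not support.

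**Conclusion.** The point holds. With ES read as Cohen's f, the stated inputs require 72 evaluable participants (85 enrolled), and 61 enrolled with about 52 completers gives about 66% power on the stated interaction test. The best case on that test, with no drop-out, is 73%. On a T0-adjusted ANCOVA the figure is about 75.5% at 52 completers, so the claimed 80% is not reached on either basis once the article's own drop-out is applied.

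The size of the shortfall rests on the f reading, on the correlation of 0.6 and on 15% drop-out without later assessment. It would be too strong to say that the trial's actual analysis has 66% power: that figure belongs to the ANOVA interaction in the sample size section.

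**What to change.** 1. Check the drop-out step, and print the effect-size metric and the values actually entered in G*Power.
2. Keep 61 as the target and restate what it delivers with about 52 completers, on one of two bases:
   - the stated ANOVA interaction: about 66% power for f = 0.15, or 80% power for f of about 0.177;
   - a T0-adjusted ANCOVA: about 75% power for a between-arm difference of 0.60 SD, or 80% power for about 0.63 SD.
3. Remove or qualify the Discussion's description of the trial as well powered.
4. Optionally, add the between-arm equivalent (4f = 0.60 SD) beside the effect size.

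The cost is wording in two sections and a less favourable stated power, with no extra participants. Preserving 80% power on the stated test would instead mean 85 enrolled, 24 more than planned. The study status section reports 23 recruited in roughly the first year, so that is about one further year at the same pace.
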